**Methods:**

Ninety eligible participants will be recruited to receive intervention at Shanghai Mental Health Center. Treatment will be randomly assigned in a double-blind fashion. Participants will receive either DLPFC (*n* = 30), OFC (n = 30), or sham (n = 30) tDCS, while continuing their usual pharmacotherapy at a stable dosage for at least 2 weeks before enrollment and throughout the stimulation period. All participants will receive 20 weekday stimulation sessions of 60 minutes duration each. Participants in the active group will be stimulated at 2 mA throughout the session, whereas the sham group will receive only a brief period of stimulation to mimic the sensation. After 20 stimulation sessions, no further treatment will be administered. Measurements will be conducted at regular points throughout and at 8 weeks after trial completion. The primary outcome is the change in the 17-item Hamilton Depression Rating Scale (HAMD-17) score after 20 sessions. Secondary outcomes were defined as changes in other measurement scales, cognitive function, resting-state functional magnetic resonance imaging (rs-fMRI), and serum biomarkers.

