### Interventions

Participants will receive one of three interventions: active DLPFC tDCS, active OFC tDCS, and sham tDCS. tDCS-CT devices (Neuroelectrics, Starstim 8, USA) will be used for brain stimulation. The anode and cathode electrodes will be inserted in saline-soaked sponges with a diameter of 3.2 cm and then positioned over the left and right DLPFC and OFC simultaneously while using a specific headgear [15] to maintain the double blind. The current will pass through the anode and cathode corresponding to the left and right DLPFC in the active DLPFC tDCS group and the left and right OFC in the active OFC tDCS group, respectively. For the sham group, the current will be rapidly increased up to 2 mA over the first 30 s then rapidly ramped down to 0 mA over the next 30 s automatically to allow participants to feel the typical initial sensations of active tDCS. At each session, a 2 mA current will be applied for a duration of 60 min. Participants will receive a total of 20 sessions, which will be conducted daily on weekdays. Trained psychiatrists and psychologists who will be blinded to the group assignments, will administer the tDCS regimen. After completing the 20 sessions, no additional stimulation treatment will be administered.

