### Data collection methods

#### Primary study parameter/endpoint

*HAMD-17*: The primary outcome criterion is the reductive ratio of the HAMD-17 score after one, two and 4 weeks of treatment. Treatment response is defined as a 50% reduction in the HAMD-17 score, and remission as a 75% reduction at any point during the 12-week trial compared with the baseline.

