### Statistical methods

Descriptive analyses will consist of means and SD for continuous variables and percentages for categorical variables. Data normality will be tested with the results expressed as mean ± SD or percentage, whenever appropriate. Nonparametric tests are to be used if the data are not normally distributed. Baseline variables will be compared between the groups using either the Student’s t-test or chi-squared test (e.g., sociodemographic data, cognitive function data, biomarkers representing inflammatory mechanisms associated with TRD, and response and remission rates among groups). To compare the primary endpoint, a two-way ANOVA will be used, considering the group (intervention and sham control groups) and time points (pre- and post-intervention), followed by the Bonferroni post hoc test, in case of significant F-ratios. A mixed-effects model for repeated measures will analyze changes from baseline HAMD-17 scores, time, and their interaction. Pretreatment values (e.g., age, sex, baseline HAMD-17, and biomarker levels) will be adopted as covariates to correct for possible differences. An intention-to-treat analysis will be conducted, that is, all participants will be included in the final analysis regardless of adherence to the intervention. No additional analyses will be performed for this study. All calculations are to be performed using R software (version 4.1.3), and the significance level is set at *p* ≤ 0.05.

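### Remission, and on the natural reading response, may be reached at any time in 12 weeks, which does not match the 4-week objective and makes the rates depend on the number of ratings

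*Protocol article*

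**What the plan says.** Under Primary study parameter/endpoint, one sentence gives both binary outcomes. It begins "Treatment response is defined as a 50% reduction in the HAMD-17 score" and ends "remission as a 75% reduction at any point during the 12-week trial compared with the baseline". No visit is fixed and no confirming rating is required.

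The sentence before it uses a different window: "The primary outcome criterion is the reductive ratio of the HAMD-17 score after one, two and 4 weeks of treatment". The abstract's Methods paragraph is narrower still: "The primary outcome is the change in the 17-item Hamilton Depression Rating Scale (HAMD-17) score after 20 sessions". The Objectives section sets the primary objective as the efficacy of a 4-week treatment, and the Outcomes section also refers to 4 weeks and 20 sessions.

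The Interventions section states: "After completing the 20 sessions, no additional stimulation treatment will be administered". The Trial design section gives a total duration of 12 weeks.

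Statistical methods lists "response and remission rates among groups" among its examples of baseline variables to be compared by t-test or chi-squared test.

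**The concern.** A best-ever rule takes the most favourable of several noisy ratings, which has three consequences.

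- A patient who crosses the threshold once and has lost the improvement by week 4 or week 12 still counts.
- A first crossing in weeks 5 to 12, with no stimulation being given, counts the same as one at the end of treatment.
- The chance of crossing at least once cannot fall as ratings are added, so the rate depends partly on how many visits a patient attends.

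A reader will take a response rate in a trial of a 4-week course as the status after that course. Under this definition it is not, and it cannot be set beside the week-4 HAMD-17 result as its binary counterpart.

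The placement in Statistical methods adds a drafting error: response and remission are post-treatment outcomes and cannot be baseline variables.

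**Working it through.** **Window.** 20 weekday sessions / 5 per week = 4 weeks of stimulation. The abstract adds "Measurements will be conducted at regular points throughout and at 8 weeks after trial completion". Reading completion there as the end of stimulation, 4 + 8 = 12 weeks, which reproduces the stated duration. So 8 / 12, two thirds of the window, lies after stimulation.

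**Number of ratings.** The text supports at least four post-baseline ratings: weeks 1, 2, 4 and 12. The content of Table 1 is not available here; more visits would enlarge the effect.

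**Assumptions (none is in the document).** Percentage reduction is normal with mean 30% at week 4, SD 25 or 30 points, and equal correlation of 0.5, 0.7 or 0.85 between visits. The mean is either flat (30% at every visit) or rising (15, 22, 30, 30%). Results for any visit come from simulating 400,000 patients per setting.

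**Single visit.** P(response) = 1 − Φ((50 − 30)/SD):
- SD 25: 1 − Φ(0.80) = 21.2%
- SD 30: 1 − Φ(0.67) = 25.2%

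P(remission) = 1 − Φ((75 − 30)/SD):
- SD 25: 1 − Φ(1.80) = 3.6%
- SD 30: 1 − Φ(1.50) = 6.7%

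**Any of four visits** (at correlation 0.5 / 0.7 / 0.85):

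| SD, mean over time | Response at week 4 | Response at any visit | Remission at any visit |
|---|---|---|---|
| 25, flat | 21% | 46 / 40 / 34% | 10.8 / 9.0 / 7.2% |
| 25, rising | 21% | 39 / 33 / 29% | 7.8 / 6.7 / 5.7% |
| 30, flat | 25% | 53 / 45 / 39% | 18.5 / 15.4 / 12.6% |
| 30, rising | 25% | 46 / 40 / 34% | 14.4 / 12.2 / 10.2% |

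**Any-visit responders who are not responders at week 4.** Every week-4 responder is also an any-visit responder, so the share is 1 − P(week 4)/P(any).
- Highest: 1 − 0.212/0.462 = 54%.
- Lowest: 1 − 0.252/0.341 = 26%.

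**Contribution of week 12** (SD 25, correlation 0.7). Adding it to weeks 1, 2 and 4 raises response from 36% to 40% with a flat mean, and from 27% to 33% with a rising mean.

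**Attendance** (SD 25, flat mean, correlation 0.7). With identical patients, 1 / 2 / 3 / 4 attended visits give 21 / 30 / 36 / 40% response. If 20% of one arm (the dropout rate in the Sample size section) left after the first visit and nobody left the other, the first arm would show 0.8 × 40 + 0.2 × 21 = 36% against 40%. That is a gap of about 4 points with no treatment effect.

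**Contrast between arms.** Sham means 15, 22, 30, 30%; active means 22, 33, 45%, then 45% at week 12 (effect persists) or 30% (effect gone). Over both SDs and all three correlations:
- week-4 gap: 18 to 21 points
- any-visit gap, effect persists: 19 to 25 points
- any-visit gap, effect gone by week 12: 14 to 17 points

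For a similar illustration at 30 per arm (SD 25, correlation 0.7), power is about 41% for week-4 response (21% v 42%). For any-visit response it is about 44% if the effect persists (33% v 57%) and about 24% if it fades (33% v 49%).

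**The case against.** **Not the primary outcome.** Response and remission are not named as primary and do not appear in the secondary lists. The primary HAMD-17 comparison is untouched. This stands and limits the weight of the point.

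**Follow-up is intended.** The Discussion says that measurements after treatment serve to describe persistence. That is a fair aim, but a best-ever rate does not measure persistence; status at week 12 does.

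**The inputs are assumed.** This also stands. A flat mean and low correlation give the upper end of the range; gradual improvement and a correlation of 0.85 give the lower end. The direction does not depend on these choices.

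A reader might also infer more than the document supports:

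- *That the rule compresses the treatment contrast.* Higher rates in both arms do not imply a smaller difference. Above, the gap is slightly larger if the effect persists and smaller only if it fades.
- *That it inflates type I error or favours one arm.* With equal attendance it does neither. Bias between arms needs unequal attendance, which the document does not predict.
- *That a purely relative remission threshold is an error.* It is an explicit definition. Showing remission against a fixed score as well, or using adjusted logistic regression, is a preference.
- *That missing week-4 ratings should simply count as non-response.* As the main method this restores the attendance penalty: with 20% missing, 21% becomes 0.8 × 21 = 17%, again about 4 points.

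**Conclusion.** The definition should be changed. As written, remission (and on the natural reading response) is a best-ever outcome over a window of which two thirds follows the end of stimulation, while the objective and the primary outcome concern the 4-week course. If the time phrase belongs to remission only, response has no time point, which also needs correcting.

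Under the stated assumptions, week-4 response of 21-25% is reported as about 29-53%, and remission of about 4-7% as about 6-18%. Roughly a quarter to a half of those counted as responders are not responders at the end of treatment. That the rates rise, and rise with visits attended, is certain; the amounts rest on an assumed mean, SD, correlation and visit schedule.

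The point is moderate. It concerns what the reported rates mean, and a possible bias if attendance differs between arms. It does not affect the validity of the primary test.

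**What to change.** - Define response (at least 50% reduction) and remission (at least 75% reduction) at the week-4 visit after 20 sessions.
- Report week-12 status separately as durability.
- Handle missing week-4 ratings by a method in which attendance does not drive the result, for example multiple imputation consistent with the planned mixed-effects model, with non-responder imputation as a sensitivity analysis.
- In Statistical methods, take the response and remission rates out of the baseline-comparison sentence and state their comparison as an outcome analysis.

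Cost: no added visits or data. The reported percentages will be lower. Because recruitment has started and the protocol requires a formal amendment for any modification, a short amendment is needed.

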#### Secondary study parameters/endpoints

Mini International Neuropsychiatric Interview (MINI);Montgomery–Asberg Depression Rating Scale (MADRS) and Oxford Depression Questionnaire (ODQ);YMRS;Clinical Global Impression Scale (CGI);Sheehan Disability Scale (SDS);WCST and SCWT;Peripheral venous blood: Biomarkers representing the inflammatory mechanisms associated with TRD will be assessed. Peripheral blood serum are to be collected and stored at − 80 °C after centrifugation. We will assess the NGF, BDNF, GDNF, IL, TNF-α, sTNFr1, and sTNFr2 levels. Serum NLR, MLR, and PLR using ELISA.rs-fMRI: Patients will also receive two rs-fMRI scan sessions before the start of treatment and after 20 stimulation sessions. A rs-fMRI scan was then performed. A diffusion tensor imaging (DTI) scan with two rs-fMRI tasks was performed to assess connectivity changes after treatment.

### Participant timeline

All time points for the physical examinations, scale assessments, medication use inventories, and laboratory examinations are shown in Table 1.

**Table 1 Tab1:**
[figure not shown]
Data collection methods and clinical assessment time points

### Data management

In the tDCS study, all data will be entered electronically. All data management work will be conducted at Shanghai Mental Health Center. A special database will be built to record all data related to the tDCS study. A complete backup of the primary database will be performed once per month.

### Data monitoring

A Data Monitoring Committee (DMC) has been established. The DMC is independent of the study organizers. Interim analyses of the primary endpoint when 30 and 70% of patients have been randomised and have completed the 12-week follow-up, respectively, will be performed by an independent statistician, who will report independently to the DMC.

### Statistical methods

Descriptive analyses will consist of means and SD for continuous variables and percentages for categorical variables. Data normality will be tested with the results expressed as mean ± SD or percentage, whenever appropriate. Nonparametric tests are to be used if the data are not normally distributed. Baseline variables will be compared between the groups using either the Student’s t-test or chi-squared test (e.g., sociodemographic data, cognitive function data, biomarkers representing inflammatory mechanisms associated with TRD, and response and remission rates among groups). To compare the primary endpoint, a two-way ANOVA will be used, considering the group (intervention and sham control groups) and time points (pre- and post-intervention), followed by the Bonferroni post hoc test, in case of significant F-ratios. A mixed-effects model for repeated measures will analyze changes from baseline HAMD-17 scores, time, and their interaction. Pretreatment values (e.g., age, sex, baseline HAMD-17, and biomarker levels) will be adopted as covariates to correct for possible differences. An intention-to-treat analysis will be conducted, that is, all participants will be included in the final analysis regardless of adherence to the intervention. No additional analyses will be performed for this study. All calculations are to be performed using R software (version 4.1.3), and the significance level is set at *p* ≤ 0.05.

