**Discussion:**

We hypothesize that, in contrast to the sham group, both the active DLPFC and OFC tDCS groups will show superiority in HAMD-17 score reduction after 5, 10, and 20 sessions. Moreover, associations of the improvement of depressive symptoms with variations in rs-fMRI and TRD-related biomarkers will be evaluated. Our study may suggest that adjunctive intensive tDCS with left DLPFC positive stimulation or right OFC negative stimulation may be effective as a novel method to relieve depressive symptoms in patients with TRD. The variation of rs-fMRI, biomarkers could be used as a potential prediction model of treatment efficacy in TRD.

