### Outcomes

Primary outcome: The reductive ratio of HAMD-17 after 4 weeks, as well as after 20 sessions.

Secondary outcomes: The changes in other clinical assessments such as the Young Mania Rating Scale (YMRS), Clinical Global Impression Scale (CGI), cognitive function, biomarkers representing potential mechanisms associated with TRD, and neuronal activity measured using rs-fMRI.

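### The primary two-way pre/post ANOVA does not say which F-test decides, does not fit the ratio endpoint or the two-arm hypothesis, and the mixed model beside it names no treatment term

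*Protocol article*

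**What the plan says.** All the analysis text is in the protocol article, Statistical methods.

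- **Primary analysis.** The method tied to the main outcome reads: "a two-way ANOVA will be used, considering the group (intervention and sham control groups) and time points (pre- and post-intervention"). The section does not name the interaction, or say that time is within-patient.
- **Follow-up tests.** The ANOVA is to be "followed by the Bonferroni post hoc test, in case of significant F-ratios". Which F is meant is not stated.
- **Second model.** "A mixed-effects model for repeated measures will analyze changes from baseline HAMD-17 scores, time, and their interaction". Treatment group is not among the terms.
- **Covariates.** "Pretreatment values (e.g., age, sex, baseline HAMD-17, and biomarker levels) will be adopted as covariates to correct for possible differences". The model they enter is not stated.
- **Distribution.** "Nonparametric tests are to be used if the data are not normally distributed". The section does not say which analyses this covers.

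The endpoint and the hypothesis are set elsewhere:

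- **Outcomes:** "The reductive ratio of HAMD-17 after 4 weeks, as well as after 20 sessions".
- **Primary study parameter/endpoint:** "The primary outcome criterion is the reductive ratio of the HAMD-17 score after one, two and 4 weeks of treatment".
- **Abstract, Methods:** the primary outcome is the change in HAMD-17 score after 20 sessions.
- **Abstract, Discussion:** "both the active DLPFC and OFC tDCS groups will show superiority in HAMD-17 score reduction after 5, 10, and 20 sessions".

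**The concern.** A two-way group-by-time ANOVA produces three F-tests: group, time and their interaction. Only the interaction asks whether the arms changed differently. If any significant F may open the post hoc tests, the claim of efficacy could rest on a test that dilutes the effect (group) or on one that says nothing about treatment (time).

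The analysis also does not match what it is meant to test. A reductive ratio is computed from baseline and follow-up together, so it has no pre-treatment value and cannot be crossed with a pre/post factor. A two-level time factor cannot address three post-baseline time points. The mixed model could have supplied the missing contrasts, but as worded it yields no treatment estimate.

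At stake is whether the trial has one primary test fixed before the data are seen, and how much of the information in 72 evaluable patients that test uses.

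**Working it through.** **Inputs from the article.** Three arms at 1:1:1 (Trial design); 24 per group, 72 in total, before dropout (Sample size); significance level 0.05 (Statistical methods). The article gives no power figure for the two-way ANOVA, so there is none to reproduce. The 24 per group is taken as given; how it was derived is a separate question.

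**Assumed, because the article does not give them.** Pre and post SD of 1; pre/post correlation ρ of 0.3, 0.5 or 0.7; true benefit of 0 or 0.8 SD in both active arms; a common fall of 1.5 SD in every arm; complete data.

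**Step 1: what each F-test estimates (active minus sham, size of benefit).**
- Group main effect: (0 + 0.80)/2 = 0.40, because there is no effect at baseline.
- Group-by-time interaction: 0.80 − 0 = 0.80, the difference in change.
- Time main effect: the average fall over all arms, which is not a treatment contrast.

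**Step 2: how often the time F is significant without a treatment effect.** With time as a repeated measure, its t statistic is centred on about 1.5/√(2(1−ρ)/72). At ρ = 0.5 this is 1.5/√(1/72) = 12.7. In 20,000 simulated null trials per setting, the time F was significant in 100% at all three correlations. (The simulation computed this F with the pooled error term; the repeated-measures value of 12.7 leads to the same conclusion.)

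**Step 3: efficiency on the charitable reading.** The interaction F is a one-way ANOVA on change, with variance 2(1−ρ). Baseline-adjusted ANCOVA has residual variance 1−ρ². Their ratio is 2/(1+ρ).

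With arm effects 0, 0.8 and 0.8, the between-arm sum of squares is 24 × (0.533² + 2 × 0.267²) = 10.24. Dividing by the variance gives the noncentrality. For the group main effect the sum of squares is 10.24/4 = 2.56 and the variance is (1+ρ)/2.

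| ρ | Variance ratio 2/(1+ρ) | Noncentrality: group / interaction / ANCOVA | Power: group main effect | Power: interaction | Power: ANCOVA |
|---|---|---|---|---|---|
| 0.3 | 1.54 | 3.9 / 7.3 / 11.3 | 39% | 65% | 84% |
| 0.5 | 1.33 | 3.4 / 10.2 / 13.7 | 35% | 81% | 91% |
| 0.7 | 1.18 | 3.0 / 17.1 / 20.1 | 31% | 96% | 98% |

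Powers are omnibus at 0.05, from 20,000 simulated trials per setting. Under the null, the repeated-measures interaction and ANCOVA both reject about 5% of the time.

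**Step 4: the analysis against the endpoint and the hypothesis.**
- Endpoint: a reductive ratio. Analysis: a factor with a pre and a post level. A ratio has no pre level.
- Hypothesis: three post-baseline time points (5, 10 and 20 weekday sessions, that is weeks 1, 2 and 4). Analysis: one post level.
- Hypothesis: each active arm against sham. Analysis: these two contrasts are not named.
- Mixed model: change from baseline is the response. The remaining named term is time, so the stated interaction has no second factor and no coefficient estimates a treatment difference.

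**The case against.** The strongest defence is that a two-way ANOVA on group and pre/post time ordinarily includes the interaction, with time within-patient. On that reading the test is unbiased, has correct type I error, and loses only efficiency. **This stands.** It rules out saying that the plan tests the wrong contrast: the plan leaves the contrast open.

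The article also lists baseline HAMD-17 as a covariate. If it enters the primary model, much of the efficiency gap closes. That is fair, but the article does not say which model the covariates enter. The missing treatment term in the mixed model also looks like a drafting slip; with treatment and treatment-by-visit restored, that model would be sound.

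A reader might infer several stronger points that the article does not support:

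- **Independent rows.** If pre and post scores were analysed as unrelated observations, the null rejection rate at ρ = 0.5 would be about 13% for the group F and 0.3% for the interaction, and interaction power would be about 44%. Nothing in the text says this will be done.
- **Pooled active arms.** The group wording could be read as intervention against sham. Trial design, Interventions and Treatment allocation all define three arms, and a Bonferroni post hoc test between groups has a purpose only with more than two. Three levels is the natural reading.
- **False positives from the time effect.** The 100% is how often the time F is significant. It is not an error rate for the arm comparisons, which would still be tested with Bonferroni adjustment.
- **Two rival primary models.** Only the ANOVA is tied to the primary endpoint.
- **Harm from the normality rule, biomarker covariates or dropped patients.** The nonparametric sentence sits beside the descriptive text and is not said to replace the primary model. Biomarkers appear only as an example. The article states intention to treat, and missing-data detail may sit in the analysis plan. No loss has been calculated for any of these.

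**Conclusion.** The concern holds in a limited form. The stated primary analysis leaves the decisive F-test open among three that answer different questions. It does not fit the ratio endpoint or the hypothesis for each active arm at three time points, and the mixed model as worded gives no treatment estimate. These are faults in what the article states, and do not depend on detail an analysis plan might add.

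The size depends on the reading. If the group main effect were used, the estimate would be half the true effect and power 31% to 39%. If the repeated-measures interaction is decisive, the analysis is valid, and the loss against baseline adjustment is 19, 10 and 2 percentage points of omnibus power at ρ = 0.3, 0.5 and 0.7. These figures assume 24 per arm, a 0.8 SD effect in both active arms, and no baseline covariate in the ANOVA. The halving of the group effect needs none of the assumed correlations or trends. The near-certain time effect needs only a clear common fall in scores.

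**What to change.** Replace the two-way ANOVA and its F gate with one primary analysis:

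1. A mixed model for repeated measures on HAMD-17 change at weeks 1, 2 and 4 in all randomised patients, with treatment (DLPFC, OFC, sham), visit, treatment-by-visit and baseline HAMD-17. Covariance structure and further terms can be left to the analysis plan.
2. Two primary contrasts at week 4, DLPFC minus sham and OFC minus sham, with Bonferroni or Holm control and no preliminary omnibus test.
3. One primary outcome scale. The Abstract says change in score; Outcomes and Primary study parameter/endpoint say reductive ratio. Choose one and use it throughout. The model above assumes change.
4. Weeks 1 and 2 labelled as secondary time points, so that the primary claim rests on week 4.
5. Rank-based tests kept as sensitivity analyses, and biomarkers kept out of the primary model.

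The cost is analysis wording and a formal amendment. No additional patients, visits or measurements are needed.

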## Methods

### Objectives

The primary objective of this study is to investigate the efficacy of a 4-week treatment of intensive adjunctive tDCS with left DLPFC positive stimulation or right OFC negative stimulation on depressive symptoms as measured by the 17-item Hamilton Depression Rating Scale (HAMD-17).

The secondary objectives are as follows:To investigate the effects of adjunctive treatment of TRD with intensive tDCS on cognition, measured by the Wisconsin card sorting test (WCST) and Stroop color–word test (SCWT).To investigate the effects of adjunctive treatment of TRD with intensive tDCS on variations in nerve growth factor (NGF), brain-derived neurotrophic factor (BDNF), glial cell line-derived neurotrophic factor (GDNF), interleukins (IL), tumor necrosis factor-alpha (TNF-α), and its soluble receptors sTNFr1 and sTNFr2 in blood plasma.To investigate the effects of combined treatment of TRD with intensive tDCS on the variation of neuronal activity in the cerebral cortex as measured by rs-fMRI.

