### Trial design

We have adopted a randomized allocation design to test sham-controlled antidepressant augmentation. Patients with TRD will continue maintenance pharmacotherapy for at least 2 weeks before stimulation initiation and during the entire stimulation period. Groups will be randomized through random code generator software (www.randomization.com) at a ratio of 1:1:1 into one of the following three groups: active DLPFC tDCS group, active OFC tDCS group, or sham tDCS group. The total study duration will be 12 weeks (Fig. 1).

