### Sample size

The sample size was calculated based on the data from O’Doherty et al. (2001) [11] and Cieslik et al. (2013) [16]. In these studies, active tDCS was assumed to be superior to sham tDCS in controlling depression with a conservative mean difference of 0.65 and standard deviation (SD) = 0.25. We set a type 1 error α (significance) and a power of 80%. The G power software (V3.1.9.4) was used to calculate the sample size. The results indicated a minimum requirement of 24 participants per group (a total of 72 participants). Accounting for a 20% dropout rate, 87 participants are required for our experiment. Finally, we plan to enroll 30 participants per group for a total of 90 participants.

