This study has several practical limitations that may affect the results. With regard to the treatment modality, delivering tDCS in a hospital setting will impose a minimal burden on inpatients; however, outpatients will have to be functional enough to use transport and to attend the hospital on a daily basis. Subsequently, there is a risk that the study population may miss outpatients with severe depression. The need for daily travel to a hospital can also lead to problems in participant compliance due to costs. We may require funding in future studies to mitigate this, as funding limitations have prevented us from employing this approach in this trial. Second, our blinding procedure follows that used in most other tDCS studies, yet recent evidence suggests that this may be insufficient to mitigate the placebo effect. Turi et al. (2019) [18] showed that healthy volunteers were able to distinguish the fade-in, short stimulation, and fade-out method of sham stimulation, described above, from true active stimulation at a level significantly greater than chance. It is not yet known how generalizable these findings are to a population with depression, but there is a need for more research on alternative methods of blinding in tDCS studies.

In conclusion, this trial is a pragmatic randomized double-blinded sham-controlled study that seeks to compare the impact of adjunctive intensive tDCS with left DLPFC positive stimulation or right OFC negative stimulation versus sham tDCS in treating patients with TRD. To our knowledge, this study is the first tDCS protocol of different stimulation targets in this patient population and the first to employ detailed measures of depressive symptoms combined with biomarkers and rs-fMRI data, which will also be used in future analyses. Given the immense health and socioeconomic impacts of TRD, new and effective treatments beyond pharmacotherapy and psychotherapy are needed; tDCS may prove useful in this regard.

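### The group factor of the primary ANOVA is labelled intervention and sham, which does not match the three randomised arms or the per-target hypothesis, and the post hoc comparisons are not named

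*Protocol article*

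**What the plan says.** Trial design: patients are allocated "at a ratio of 1:1:1 into one of the following three groups: active DLPFC tDCS group, active OFC tDCS group, or sham tDCS group".

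Abstract, Discussion: compared with sham, "both the active DLPFC and OFC tDCS groups will show superiority in HAMD-17 score reduction after 5, 10, and 20 sessions". This is a statement about each target separately.

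Statistical methods: the primary endpoint goes into a two-way ANOVA, "considering the group (intervention and sham control groups) and time points (pre- and post-intervention), followed by the Bonferroni post hoc test". The post hoc step is conditional: "followed by the Bonferroni post hoc test, in case of significant F-ratios". The comparisons in that step are neither listed nor counted. A second model is mentioned, "A mixed-effects model for repeated measures will analyze changes from baseline HAMD-17 scores, time, and their interaction", but no contrast between arms is named there either. The significance level is 0.05.

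Sample size: 24 per group are required, and 30 per group are enrolled to allow for 20% dropout (30 × 0.8 = 24).

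**The concern.** The label on the group factor fits a two-group trial. If an analyst follows it as written, DLPFC and OFC patients form one intervention group. A significant result could then come from one target alone and be reported for both. A real effect of one target could also be missed because it is averaged with an inactive arm. Either way, the per-target hypothesis in the Abstract is not tested.

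If the analyst takes group to have three levels, the pooling disappears, but the claims then rest on a post hoc step with an unspecified set of comparisons that can be reached only through a significant F. The two comparisons with sham may therefore be tested more strictly than needed, or not tested at all.

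**Working it through.** **1. Effect size to use.** The Sample size section gives a mean difference of 0.65 and SD 0.25, so d = 0.65/0.25 = 2.6. The normal formula gives n = 2(1.96 + 0.84)²/2.6² = 15.68/6.76 = 2.3, so 3 per arm, not the stated 24. The plan's figure is not reproduced, and it supplies no usable effect size. The effects below are assumptions in SD units.

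**2. Set-up.** There are n patients per arm, residual SD 1 and a variance estimated from all three arms (df = 3n − 3); tests are two-sided at 0.05. This is a one-time-point comparison that simplifies the two-way ANOVA.
- Pooled contrast: estimate (d₁ + d₂)/2, standard error √(1/n + 1/(2n)) = √(1.5/n).
- One arm against sham: standard error √(2/n).

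**3. Literal reading, only one target works (d = 0.8 and 0, n = 24).**
- Pooled: (0.8 + 0)/2 = 0.4; standard error √(1.5/24) = 0.25; noncentrality 0.4/0.25 = 1.6; critical t (69 df) 1.995; power 0.35.
- Effective arm alone: 0.8/√(2/24) = 0.8/0.2887 = 2.77. Simulated power is 0.69 by Holm over the two sham contrasts (0.686) and 0.62 by a significant F followed by Bonferroni over three pairs.

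**4. Three-level reading, both targets work (d = 0.8 and 0.8).** Simulated power, comparing F then Bonferroni over three pairs with Holm over the two sham contrasts:

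| | F, then Bonferroni ×3 | Holm ×2 |
|---|---|---|
| 24 per arm, a given arm | 0.62 | 0.74 |
| 24 per arm, both arms | 0.47 | 0.65 |
| 30 per arm, a given arm | 0.74 | 0.84 |
| 30 per arm, both arms | 0.61 | 0.77 |

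With 30 per arm and only one target working, the two rules give 0.74 and 0.79, a gap of about 5 points.

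**5. Same data, different reading (30 per arm, df = 87).**
- Observed effects 0.65 and 0: pooled t = 0.325/√(1.5/30) = 1.45, p = 0.15. The better arm has t = 0.65/√(2/30) = 2.52, p = 0.014, or 0.027 after doubling and 0.041 after tripling; F gives p = 0.018. The pooled reading fails and the arm-wise reading succeeds.
- Observed effects 0.5 and 0.5: pooled t = 0.5/√(1.5/30) = 2.24, p = 0.028. The three-level F gives p = 0.088, so the post hoc step is never reached. The pooled reading succeeds and the arm-wise reading fails.

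**6. Sensitivity to the assumed effect, one target working.** With 0.65 SD at 30 per arm, pooled power is 0.30 and F-gated Bonferroni ×3 gives 0.53. With 0.83 SD at 24 per arm, they are 0.37 and 0.66. At d = 2.6 the pooled noncentrality is 1.3/0.25 = 5.2, so power is close to 1 under either reading; pooling would still not identify the effective target.

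**The case against.** The best defence is that three levels were intended. The plural in "considering the group (intervention and sham control groups) and time points (pre- and post-intervention), followed by the Bonferroni post hoc test" can cover two intervention groups plus sham, a post hoc test has little use for a two-level factor, and the rest of the article describes three groups. This is a fair reading, and it means the article cannot be said to prespecify a pooled analysis. It does not cure the wording: the literal reading remains open, and the same section compares continuous baseline variables by Student's t-test, which is also a two-group method.

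A reader might further infer several rival success rules: pooled from the Sample size section ("active tDCS was assumed to be superior to sham tDCS in controlling depression"), either arm from the Objectives ("intensive adjunctive tDCS with left DLPFC positive stimulation or right OFC negative stimulation on depressive symptoms"), and target against target from the Discussion ("this study is the first tDCS protocol of different stimulation targets in this patient population"). The documents do not support this. The first describes an effect attributed to cited studies, and the resulting size is given per group. The second lists the two interventions. The third is a claim of novelty. The Abstract does point to the two sham contrasts.

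The article does not say that Bonferroni covers three comparisons; that is one possibility. If it covers only the two sham contrasts, most of the loss goes when one target works (at 24 per arm, ungated, 0.68 against 0.69 by Holm). Bonferroni is also a valid method, so preferring Holm or Dunnett is a matter of efficiency. Finally, a comparison family is often left to an analysis plan. That would excuse silence, but here the article states a factor label and an F gate that fit the design badly.

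**Conclusion.** The concern stands as a mismatch between the stated primary analysis and the design, and it should be corrected. Followed literally, the analysis cannot answer the per-target question at any effect size. The power cost depends on assumption: with 0.8 SD in one arm only and 24 per arm, 0.35 against about 0.69. Under the three-level reading the cost is smaller and arises only if all three pairs share the Bonferroni correction: about 12 points per arm and 18 points for both arms at 24 per arm, and less at 30.

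Two stronger conclusions do not follow. The article does not clearly commit to pooling. Nor is a significant pooled test beside a non-significant weaker arm in itself a contradiction, since a weaker arm will often miss significance simply through low power. The harm is an undefined basis for the claim and avoidable loss of power, not demonstrated bias.

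**What to change.** In Statistical methods, replace the two-label description of group with the three randomised arms. Name DLPFC versus sham and OFC versus sham as the two primary contrasts at the single primary time point (the Abstract gives it as after 20 sessions). Test them by Holm or Dunnett at an overall two-sided 0.05, without requiring a significant F first. State that each target is claimed effective only on its own adjusted contrast. Report DLPFC versus OFC, and any pooled active-versus-sham comparison, as secondary estimates with 95% confidence intervals.

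This needs no further patients, visits or data; it is a change of wording in the protocol and the analysis plan. The price is that the pooled comparison and the comparison between targets can no longer carry the primary claim.
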